#### Usual care

The control arm receives standard care, that is, they have access to their oncologist and clinical nurse specialist, as well as cancer information and support services. Treatments and services accessed during the treatment phase are logged at post-treatment assessment. The usual care group are offered a form of CBT off-trial at the end of the trial.

### Measures

The measures taken at each stage of the trial are summarised in table 2.

**Table 2 T2:** Study measures

Phase	Pre-baseline	A0 Baseline assessment	Treatment phase	A1 Post-treatment assessment	A2 Follow up assessment
**Interview measures**					
Medical history incl. breast cancer treatment, menopause symptoms, concomitant medications and therapies		X			
**Questionnaire measures**					
Weekly diaries	X^1^		X^2^		
Demographics: Age, BMI, ethnicity, parity, marital status, education, employment, smoking, drinking, exercise		X			
Hot flush rating scale		X	X^2^	X	X
Hot flush beliefs scale		X		X	X
Women's health questionnaire		X		X	X
Perceived Stress Scale		X		X	X
Somatic Amplification Scale		X		X	X
SF-36		X		X	X
Life Orientation Test		X			
Use of services				X	X
CBT session evaluation				X^3^	
**24 hour monitoring**					
Sternal skin conductance		X		X	
24 hour diary		X		X	

Notes:

^1^Two weekly diaries completed prior to baseline assessment

^2^Completed each week for 6 weeks by those randomised to Group CBT only

^3^Completed by participants receiving Group CBT only

#### Socio-demographics

Socio-demographic variables include date of birth, height, weight, ethnicity, number of children, education, marital status, employment status, smoking, drinking and exercise. Breast cancer treatment, use of treatments for menopause and concomitant medications and therapies are also recorded.

#### Primary Outcome: Hot flush problem rating

Hot flush problem rating is a subscale of the Hot Flush Rating Scale [55], calculated as the mean of three items each measured on a 10 point scale (low to high), e.g. "To what extent do you regard your flushes/sweats as a problem?" (1 = not at all a problem, 10 = very much a problem).

#### Secondary Outcomes

Hot flush frequency and severity are assessed using the following measures:

##### Hot Flush Rating Scale [55]: Frequency subscale

The frequency subscale of the HFRS is a retrospective estimation of the number of HF/NS experienced in the previous week, e.g. "How often have you had hot flushes in the past week?" Average severity of HF/NS over the previous week is estimated for hot flushes and for night sweats separately (1 = mild, 2 = moderate and 3 = severe).

##### 24-hour hot flush diary

Women monitor their HF/NS prospectively for 24 hours. When they experience a hot flush or night sweat they note down the severity (1 = mild, 2 = moderate and 3 = severe) and the time at which it occurred.

##### 24-hour ambulatory sternal skin conductance and event marker

During the 24-hour diary monitoring period women wear an ambulatory SSC monitor [56]. The monitor is approximately 6 × 6 cm, with two 8 cm electrodes attached to an adhesive electrode patch by press studs. The adhesive electrode patch is attached to the sternum, two inches below the sternal notch, which holds the monitor close to the body. Skin conductance is measured by passing a pulse through the electrodes every 5 seconds, indicated by a green flash of an LED on the monitor. A hot flush is defined by an increase in conductance of 2 mmhos or more in 30 seconds, occurring no less than 15 minutes since the last SSC-defined HF/NS (i.e. 15 minute lock out period [57]). For each SSC-defined hot flush or night sweat, SSC level and the time at which it occurred are extracted for analysis. Women can indicate that they are experiencing a HF/NS by passing a magnet near to the monitor. The magnet is worn on a bracelet. The times at which the magnetic event marker is registered are summed to produce a 24 hour HF/NS frequency.

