Evaluating treatment efficacy depends on valid and reliable measures of HF/NS. The most commonly used measures of HF/NS are women's own self-reports. These include diaries, in which women note the time when a hot flush occurs and usually a severity rating (e.g. mild, moderate or severe). Electronic event markers can also provide a convenient method of registering a perceived hot flush. Sternal skin conductance (SSC) is considered to be the most valid physiological index of HF/NS [17]. A hot flush is marked by a sudden increase in skin conductivity, due to a sweat response, which tails off as sweating decreases (a 'swishy tail'). This pattern is in contrast with a 'saw-tooth' fluctuation in sweating which occurs in typical thermoregulatory control. SSC does not, however, correlate well with subjective measures of severity or problem ratings, and hot flushes defined by SSC and self-reported hot flushes are not always concordant [18]. Reasons for discordance are not well understood, but use of both measures can increase understanding of the impacts of interventions [16]. For example, self-report but not physiological measures (SSC) have shown placebo effects [19], but physiological measures are less predictive of problem ratings and help seeking than self-reports. For these reasons SSC should be used together with self-report measures (frequency and the extent to which they are problematic) [20]. SSC has not yet been used to evaluate treatments in the UK. 24 hour SSC monitoring has been piloted and has been acceptable to women [21,22].

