#### Current study

This present study aims to evaluate the effectiveness of Group CBT to alleviate HF/NS in women who have had treatment for breast cancer, comparing Group CBT and usual care in a randomised controlled trial, with both physiological and self-reported measures of HF/NS and a 6-month post-randomisation follow-up. We hypothesize that Group CBT will be more effective than usual care in reducing HF/NS problem rating and frequency. Secondary analyses will examine the effects of Group CBT on hypothesised mediating variables, including mood, quality of life, beliefs and behaviours, optimism and somatisation. If effective, the treatment can be promoted by publication of the treatment manual and by training and supervising health professionals in the application of the treatment.

The trial tests four main hypotheses:

1. There will be a significant reduction in problem rating of HF/NS following Group CBT compared to usual care.

2. There will be a significant reduction in frequency of self-reported and SSC-defined HF/NS following Group CBT compared to usual care.

3. Changes in problem rating and frequency of HF/NS following Group CBT will be maintained at six months post-randomisation.

4. There will be significant improvements in mood, beliefs and behaviours about HF/NS and quality of life following Group CBT compared to usual care.

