The treatment is compared to a usual care group to see whether it improves on current practice, but usual care control groups have some drawbacks. Usual care may vary between centres, although typically treatment is minimal. Those receiving usual care may be more likely to seek complimentary therapies if they are having no other treatment. Complementary therapy use and clinic treatments are monitored in the trial and may have to be controlled for in analysis. If usual care is minimal then it will be similar to a no-treatment control group, and treatment effects might be due to the extra attention rather than the treatment per se (i.e. any intervention is better than nothing). Transitory changes and biased reporting should be apparent by comparing self-reported HF/NS with physiological measures and post-treatment with follow up data. Early in the treatment development phase it makes sense to compare with current practice, especially as some improvement in usual care would be predicted if only because symptoms do get better in time. Should treatment effects be robust, further research into the active treatment components can be tested using attention control groups.

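### The printed threshold for an SSC-defined hot flush, 2 mmhos in 30 seconds, is probably a milli/micro slip of 1,000-fold and should be checked and corrected before events are extracted

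*Protocol article*

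**What the plan says.** Under Secondary Outcomes, the section on the ambulatory SSC monitor and event marker gives a complete counting rule: "A hot flush is defined by an increase in conductance of 2 mmhos or more in 30 seconds". A 15-minute lock-out after each counted event, with a citation, completes it. The sampling is also stated: "Skin conductance is measured by passing a pulse through the electrodes every 5 seconds". The rule decides which events enter the data: "For each SSC-defined hot flush or night sweat, SSC level and the time at which it occurred are extracted for analysis".

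The resulting count is used in three places:

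- Hypothesis 2 in the Current study section: "There will be a significant reduction in frequency of self-reported and SSC-defined HF/NS following Group CBT compared to usual care".
- The Analysis section, where the frequency of flushes defined by skin conductance is one of the mediators to be explored.
- Methodological considerations, where it serves as a safeguard for a comparison with usual care: "Transitory changes and biased reporting should be apparent by comparing self-reported HF/NS with physiological measures and post-treatment with follow up data".

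The unit appears nowhere else in the article, the list of abbreviations does not explain it, and no range for skin conductance is given.

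**The concern.** The prefix m means milli, so the printed threshold is in thousandths of a mho. A rise of that size would need the path between two electrodes on the chest to become a very good conductor within 30 seconds. If skin conductance is of the order of micromhos to tens of micromhos, which is an assumption here, no trace could meet the rule.

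This is a stated decision threshold and not a detail left to a fuller document: the article prints the amplitude, unit, time window and lock-out. If the printed unit were carried into the scoring, the SSC count would be zero for every woman at both assessments. The SSC part of hypothesis 2 could then not be tested, the mediator would be a constant, and the comparison of self-report with physiology would have nothing on one side. If the scoring is right and only the printed unit is wrong, the harm is smaller: the published definition of a key secondary outcome cannot be followed or reproduced as it stands.

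**Working it through.** The threshold is a definition, so there is no calculated figure of the plan to reproduce. The check is a unit conversion followed by a comparison with an assumed signal.

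**Inputs from the protocol article (SSC monitor section):** threshold 2 mmhos; window 30 seconds; one reading every 5 seconds; lock-out 15 minutes.

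**Input not in the article (assumption):** total skin conductance of 1 to 100 micromho. As an alternative, a largest 30-second rise of 5 to 100 micromho.

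**Step 1, conversion.** 1 mmho = 1,000 micromho, so 2 mmho = 2,000 micromho. Resistance = 1/conductance = 1/0.002 = 500 ohm. If micromho was meant, the threshold is 2 micromho, or 1/0.000002 = 500,000 ohm. The two readings differ by a factor of 1,000.

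**Step 2, rate.** A 30-second window holds 30/5 = 6 sampling intervals. The literal rule needs an average rise of 2,000/6, about 333 micromho, per interval. In micromho it needs 2/6, about 0.33.

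**Step 3, threshold against assumed total conductance.**

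| Assumed total (micromho) | Threshold / total |
|---|---|
| 1 | 2,000/1 = 2,000 |
| 100 | 2,000/100 = 20 |

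**Step 4, threshold against assumed largest 30-second rise.**

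| Assumed largest rise (micromho) | Threshold / rise |
|---|---|
| 5 | 400 |
| 10 | 200 |
| 20 | 100 |
| 50 | 40 |
| 100 | 20 |

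At every value in either table the threshold exceeds the signal at least 20-fold, so the literal rule counts nothing. For the conclusion to fail, the upper end of the assumed range would have to be too low by a factor of 20 or more. The lock-out cannot rescue the rule, because it only removes events.

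**Step 5, reach.** The Power calculation section is built on the problem rating subscale of the Hot Flush Rating Scale. Nothing in it uses SSC, so the sample size and the primary outcome are untouched.

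**The case against.** **The documents do not prove that the threshold is out of reach.** This stands. They give no conductance range and state the unit only once, so the conclusion rests on a labelled assumption. The margin of at least 20-fold means that the assumption need not be precise.

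**It may be a symbol artefact.** A micro sign can become an m in typesetting or when a PDF is read. The age stratum in the Randomisation section is printed as two separated characters, so not every symbol is set cleanly. On the other hand, the multiplication sign in the monitor's dimensions survived in the same paragraph. The possibility remains. If the artefact arose in the article itself, the published definition still needs correcting; if it arose only in reading the PDF, the point falls.

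**A printed prefix does not set the software.** This also stands. The rule carries a citation, and the Background says that 24-hour monitoring had been piloted. A reader might infer that the trial will record no flushes in either arm, or that the method cannot identify a flush. The article supports neither: the consequence holds for the rule as printed, not for the scoring actually done.

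**Tail shape.** A reader might also infer that the rule is defective because it omits the tail. The Background describes a flush trace as a sudden rise "due to a sweat response, which tails off as sweating decreases (a 'swishy tail", and adds: "This pattern is in contrast with a 'saw-tooth' fluctuation in sweating which occurs in typical thermoregulatory control". That passage describes traces and sets no scoring criterion. Nothing in the article shows that saw-tooth sweating meets the amplitude and rate conditions. Visual scoring of the tail is a measurement preference, and a condensed article may leave it to the full protocol.

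**Dilution.** Nor would extra events unaffected by treatment shrink the planned estimate. Secondary outcomes are analysed by a linear mixed model, which compares means. Adding f events per day to both sides leaves a difference unchanged: the pilot's self-reported fall is (68.2 − 46.7)/7 = 3.07 per day whatever f is. Only a percentage would change.

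**Conclusion.** The concern holds for the unit alone. As printed, the SSC threshold is 2,000 micromho, which is 20 to 2,000 times total skin conductance under an assumed range of 1 to 100 micromho, and applied literally it detects no events. The most likely explanation is a 1,000-fold milli/micro slip in the written definition. Confidence is moderate, because the conductance range is an assumption and an artefact of typesetting or PDF reading cannot be excluded. The point bears on the SSC part of hypothesis 2, one mediator and the check on reporting bias. It is a correction to a stated threshold and gives no ground for criticising SSC as a measure or the form of the counting rule.

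**What to change.** Before SSC events are extracted:

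1. Check the unit against the source cited with the rule, the unit in which the monitor exports its readings, and the threshold set in the scoring software.
2. Correct the threshold in the SSC monitor section. The expected wording is 2 micromho in 30 seconds, subject to that check. Writing the unit out in full avoids another loss of the micro sign.
3. If any traces have already been scored, record which unit was used, and rescore them if it was the wrong one.

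The cost is a short check and a one-word correction. No new data, visits or change to the analysis are needed unless traces prove to have been scored with the wrong unit, and rescoring would then use recordings already held.

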##### Health related quality of life

General physical and mental health are indexed using the *General Health Survey Short Form 36 *(SF-36) [58], a widely used 36 item health survey. Two physical and mental health summary scales are constructed, with a possible range from 0 to 100, where higher scores indicate better health [59]. Perceptions of physical and emotional symptoms are measured using the *Women's Health Questionnaire *(WHQ) [49] which is standardised on samples of mid-aged women. The WHQ contains 36 items, for example, "I feel more tired than usual", which are scored on 4-point scales. Nine subscales are formed by counting the number of items scoring 2 or 3 and dividing by the number of items for each scale, resulting in scales from 0 to 1. The WHQ has been widely used to evaluate interventions for menopausal symptoms [60].

#### Process measures

##### Beliefs about hot flushes and night sweats

HF/NS beliefs are measured using the Hot Flush Beliefs Scale [15], a 27-item scale comprising three subscales including social context, coping with hot flushes, and coping with night sweats. An additional scale is included which measures behavioural reactions to HF/NS, the Hot Flush Behaviour Scale (HFBehS).

##### Perceived stress

The Perceived Stress Scale [61] measures 10 items, for example "How often have you been upset because of something that happened unexpectedly?", on a scale from 0 (never) to 4 (very often). Items are summed to form a 0-40 scale, where 0 is low stress and 40 is high stress.

##### Somatic amplification

Barsky, Grace and Klerman's [62] Somatic Amplification Scale is a 10 item scale measuring a general tendency toward body focus, including items such as "When someone else coughs, it makes me cough too" (1 = not like me to 5 = very much like me). The mean of the 10 items is calculated resulting in a 5-point scale where 5 is high somatic amplification.

##### Dispositional optimism

The Revised Life Orientation Test (LOT R [63]) measures dispositional optimism on a 8-item scale including "In uncertain times, I usually expect the best" (0 = strongly disagree to 4 = strongly agree). A mean of all items is calculated, resulting in a 5-point scale where high scores indicate higher dispositional optimism.

##### Treatment evaluation

Participants randomised to the group CBT arm are asked to rate the usefulness of the sessions overall and of specific elements of the intervention; use of the relaxation CD, attendance and completion of homework are also being measured.

### Adverse events

An adverse events protocol has been agreed by the DMC and TSC, adapted for a non-medical trial using the Medical Research Council/Department for Health Joint Project Guideline notes on Pharmocovigilance [64]. This excludes study outcomes, such as increases in frequency or severity of HF/NS that occur as part of normal fluctuations in menopause symptoms. Adverse events are logged in the trial master file and reported to the principle investigator and trial coordinator. In accordance with the National Patient Safety Agency's requirements for reporting of serious adverse events (SAE), any adverse event deemed to be a related or unexpected SAE will be reported to the principle investigator, the sponsor and the DMC within 48 hours, and reported to the Hospital Research Ethics Committee in accordance with their procedures. Reoccurrence of breast cancer or secondary cancer does not need to be reported in this way, as it is an expected unrelated serious adverse event (see appendix 3 of the Joint Guidelines [64]). An adverse events report of these occurrences will be included in the report to the DMC in accordance with the DMC charter.

### Power calculation

The sample size is calculated on the HFRS problem rating subscale [55], estimating a mean of 5 (SD = 2.4) and a clinically relevant difference of 2 points [45] at two weeks post-treatment. A total sample size of 76, 38 in each group, will have 90% power to detect a difference in mean HF/NS Problem Rating of 2, controlling for baseline value, assuming a common standard deviation of 2.4, a correlation between baseline and end of treatment values of 0.4 (giving a correction factor of 0.84 [65]) and a 5% two-sided significance level. Due to clustering of outcomes within therapy groups, the sample size has been adjusted by assuming an intra-class correlation of 0.07 [66] and 8 participants per group giving a variance inflation factor of 1.49. Ninety six women will be recruited in to the trial to allow for a 20% attrition rate.

### Analysis

An analysis plan has been agreed (i.e. prior to completion of data collection). A trial statistician, employed by the Mental Health and Neurology Clinical Trials Unit at King's College London, carries out primary and secondary data analysis, and is blind to group allocation. Unless indicated, scales are calculated according to published scoring algorithms. All statistical tests are two sided (level of significance = 0.05). The analyses are preformed using the statistical software Stata version 11.0. An intention to treat analysis of the primary outcome is performed. Difference in problem rating between the two intervention groups is tested using a linear mixed model, utilising fixed and random effects. The regression model compares the problem rating subscale of HFRS between intervention groups, after allowing for the baseline measurements to control for pre-treatment differences, stratification factors (age: 50 years or older versus younger than 50 years), and clinically relevant covariates. Greater precision of estimates is expected within therapy groups. Therefore models are adjusted for the therapy group; this variable is able to randomly vary around the intercept (random effects). Secondary outcomes at post-treatment are analysed similarly. Follow-up data at 6 months is also explored through linear mixed models utilising repeated measures analyses, allowing simultaneous modelling of the two outcome time points. Mediation of treatment effects by hot flush beliefs and behaviours, mood, stress, quality of life and frequency of HF/NS defined by skin conductance rises will be explored using a two stage least squared method in Stata [67]. Moderation by optimism and somatisation is also tested using multiple-group modelling [68].

## Discussion

This study is a randomised controlled trial of cognitive behavioural therapy to treat hot flushes and/or night sweats experienced by women who have completed treatment for breast cancer. This non-medical treatment aims to alleviate HF/NS symptoms in women who have limited medical treatment options due to contraindications. It is a robustly designed trial, comparing six sessions of Group CBT to usual care using both self-reported and physiological outcome measures. The primary outcome is change in HF/NS problem rating at post-treatment: an average reduction in problem rating of 2 points on the HFRS problem rating subscale is needed for treatment efficacy to be considered clinically significant. The study also tests the hypotheses that Group CBT will reduce frequency of HF/NS, improve mood, sleep, general wellbeing, and beliefs about HF/NS. It is further hypothesised that these improvements will be maintained at six months post-randomisation. If this non-medical treatment is found to be successful it could be delivered in primary or secondary care settings by appropriately trained and supervised health professionals.

### Methodological considerations

The design has several strengths. The treatment has been extensively developed and piloted for feasibility, acceptability and preliminary outcomes. Preliminary results found an average 2.5 point reduction in problem rating (49% reduction) as well as a significant reduction in self-reported frequency, and significant improvements in sleep quality and quality of life were also reported [47]. A treatment manual specifies the detail for each session so that it is replicable, and checks are in place to ensure adherence to protocol. Measures of treatment efficacy are robust: as well as questionnaire-based estimations of recent symptoms, the trial includes prospective monitoring of symptoms using self-report and physiological measures. Very few trials of treatments for HF/NS include both types of prospective monitoring, and no trials of CBT for HF/NS have done so. The study sample is drawn from a socially and culturally diverse area of the UK; the uptake and adherence to the treatment by women from different backgrounds will be reported.

There are some limitations that should be considered. Recruitment procedures are designed to reach all of the symptomatic breast cancer patients who attend clinics in the South East London Network (SELCRN) hospitals. Clinic and research staff approach patients directly and posters and leaflets are placed in waiting rooms so that patients can opt in themselves. Nonetheless, the sample might not be representative of symptomatic breast cancer patients in general and we cannot know how many people were made aware of the trial through these recruitment procedures.

The treatment is compared to a usual care group to see whether it improves on current practice, but usual care control groups have some drawbacks. Usual care may vary between centres, although typically treatment is minimal. Those receiving usual care may be more likely to seek complimentary therapies if they are having no other treatment. Complementary therapy use and clinic treatments are monitored in the trial and may have to be controlled for in analysis. If usual care is minimal then it will be similar to a no-treatment control group, and treatment effects might be due to the extra attention rather than the treatment per se (i.e. any intervention is better than nothing). Transitory changes and biased reporting should be apparent by comparing self-reported HF/NS with physiological measures and post-treatment with follow up data. Early in the treatment development phase it makes sense to compare with current practice, especially as some improvement in usual care would be predicted if only because symptoms do get better in time. Should treatment effects be robust, further research into the active treatment components can be tested using attention control groups.

